### Quantitative and Qualitative Analysis and Integration

Quantitative data will be analyzed to assess the effect of the interventions on modern contraceptive uptake, client satisfaction, and service provider competence, while appropriately accounting for the clustered study design. Qualitative data from focus group discussions and in-depth interviews will be examined using thematic analysis to explore participants’ experiences, as well as key barriers and facilitators to implementation. Findings from both components will be brought together at the interpretation and reporting stage using a convergent mixed-methods approach, allowing qualitative insights to help explain and contextualize quantitative results, including differences observed across study arms and clusters.

### Study Outcomes

The primary outcome will be uptake of modern contraceptive methods, and the secondary outcome will be client satisfaction and service provider competence. Follow-up assessments will be conducted 3 and 6 months after the intervention.

### Addressing Missing Data

To minimize bias, data completeness will be closely monitored, and follow-up efforts will be made where feasible. For missing client-reported items (eg, satisfaction), multiple imputations will be used under the assumption of data missing at random. For key outcomes, such as contraceptive uptake and service provider competence, sensitivity analyses will compare imputed and nonimputed datasets. Reasons for missing data (eg, loss to follow-up) will be recorded and descriptively analyzed.

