**Figure 1. F1:**
[figure not shown]
Conceptual framework of the study.

For this study, modern methods of contraception include birth control pills, female and male sterilization, intrauterine contraceptive devices, injectable contraceptives, implants, male condoms, and emergency contraception [20]. A client-centered approach is defined as one based on understanding a woman’s fertility goals and contraceptive needs and preferences, providing education on contraceptive methods and autonomy, and encouraging open dialogue [21].

The GATHER approach for FP is a structured counseling strategy. Service providers follow the 6 steps in the approach’s name (greet, ask, tell, help, explain, and return). This structured approach helps providers build rapport, explore the goals and concerns of the client, provide tailored contraceptive information, facilitate the informed decision-making ability of the client, comprehensively explain the use of contraceptives, and, lastly, schedule a return visit for follow up [22].

The BCS is also a structured, evidence-based strategy for FP counseling. It follows three steps: (1) the pre-choice step, in which the service provider assesses the client’s needs and provides tailored information; (2) the choice of method step, in which the client and provider discuss contraceptive options and address the concerns of the client; and (3) the post-choice step, in which the provider reinforces correct use of the chosen method and provides follow-up assistance. This strategy enables decision-making and contraceptive adherence in clients and improved client satisfaction.

Effective FP counseling improves knowledge, autonomy, and contraceptive use. Key factors include clear communication, client engagement, respect for choices, and follow-up support. Success is measured by satisfaction, continued use, reduced discontinuation, and alignment with reproductive goals [23].

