### Data Collection and Analysis

Data has been collected from structured facility records and client exit interviews at baseline (before the intervention) and will be collected 3 and 6 months after the intervention. Data quality will be ensured through descriptive statistics and logical validation checks, identifying missing values, inconsistencies, and outliers. The baseline characteristics will be summarized for assessing comparability across clusters.

The quality of FP services will be assessed using the Quick Investigation of Quality tool, which measure 25 key indicators of counseling quality [27]. For the data analysis, SPSS (version 26; IBM Corp) will be used. Service provider and client characteristics will be summarized in descriptive analyses. Exploratory comparisons will use paired 2-tailed *t* tests (or Wilcoxon signed-rank tests), ANOVA, and *χ*^2^ tests.

Mixed effects regression models with a random intercept for hospital catchment (cluster) will be using for clustering. These will be used to analyze binary outcomes of the interventions, such as uptake of modern contraceptives. Mixed effects logistic regression will be applied. For continuous outcomes, such as client satisfaction and quality score, we will use mixed effects linear regression. To assess robustness, population-averaged models using generalized estimating equations with robust SEs will be considered as a sensitivity analysis.

To estimate the changes in outcome over time between the interventional and control arms, we will use a difference-in-differences approach. All multivariate models will be adjusted for individual-level covariates such as age, parity, education, and baseline contraceptive use, as well as facility-level characteristics.

Effect sizes for categorical outcomes will be reported as odds ratios with 95% CIs, and for continuous outcomes, Cohen *d* will be used. Statistical significance will be assessed at a 2-sided *P* value <.05. Results will be presented in the form of tables and graphical summaries for interpretability and for informing future scalability.

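### For uptake, the one stated missing-data sensitivity analysis sets imputed against non-imputed results; both rest on nearly the same assumption, so agreement cannot rule out bias from women who stop a method going unseen

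*Protocol article*

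**What the plan says.** All references are to the protocol article.

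- **Addressing Missing Data.** For missing client-reported items, with satisfaction as the example, "multiple imputations will be used under the assumption of data missing at random". For key outcomes, naming uptake and provider competence, "sensitivity analyses will compare imputed and nonimputed datasets". The section also says that "data completeness will be closely monitored, and follow-up efforts will be made where feasible" and that "Reasons for missing data (eg, loss to follow-up) will be recorded and descriptively analyzed".
- **Study Outcomes.** Uptake of modern methods is the primary outcome, assessed at 3 and 6 months.
- **Data Collection and Analysis.** The sources are facility records together with "client exit interviews at baseline (before the intervention) and will be collected 3 and 6 months after the intervention". A second sensitivity analysis there, generalized estimating equations with robust standard errors, addresses the clustering model and not missing data.
- **Study Framework, text after Figure 1.** A GATHER session is to end with a further step: "and, lastly, schedule a return visit for follow up". In the balanced counseling strategy (BCS), "the provider reinforces correct use of the chosen method and provides follow-up assistance"; no scheduled visit is mentioned. Table 1 gives the control arm routine counseling, with no follow-up element described.
- **Study Participants: Purposive Sampling and Sample Size Calculation.** Assumed uptake is 25% in control and 40% in the intervention arms, with 60 women per arm.

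**The concern.** A sensitivity analysis should vary the assumption that is in doubt. Here the doubtful assumption is that, given the recorded covariates, a woman's chance of being observed does not depend on whether she still uses a method. Neither side of the planned comparison relaxes it. When mainly the outcome is missing and the imputation model uses the same predictors as the analysis model, imputation adds little information and the two results will be close, whether or not both are wrong.

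Loss that depends on use is realistic in this trial. Both data sources are largely tied to contact with a facility, and a woman who has stopped her method has less reason to make contact. The section's own example of a reason for missing data is loss to follow-up. Because counseling on return and follow-up differs between arms, the pattern of loss may differ too, and it is the difference in pattern that distorts the comparison of arms. At stake is the primary estimate that the pilot would pass on to a larger study, accompanied by a check that appears to support it.

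**Working it through.** **Plan's figures.** Assumed effect: 40% − 25% = 15 points. The article gives no loss rate for the trial phase, so there is no figure to reproduce. Every loss rate below is an assumption.

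**Step 1: what the analysis sees.** Let p be true uptake, u the share of users lost and n the share of non-users lost.

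Observed uptake = p(1−u) / [p(1−u) + (1−p)(1−n)]

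**Step 2: why imputation does not repair it.** Let o be observed uptake and L the overall loss in an arm. If covariates predict stopping poorly, imputation under missing at random assigns about o to the unseen women, so the completed estimate is o(1−L) + oL = o, the complete-case value. The two differ only so far as covariates such as age, parity, education and baseline use explain the loss.

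**Step 3: no true effect, p = 25% in both arms.** The last column counts every missing woman as a non-user, which gives p(1−u) per arm. Differences are taken before rounding.

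| Case | Control u / n | Intervention u / n | Control shows | Intervention shows | False difference | Missing = non-user |
|---|---|---|---|---|---|---|
| A | 20% / 20% | 5% / 30% | 25.0% | 31.1% | +6.1 | +3.8 |
| B | 20% / 20% | 5% / 20% | 25.0% | 28.4% | +3.4 | +3.8 |
| C | 20% / 30% | 5% / 30% | 27.6% | 31.1% | +3.6 | +3.8 |
| D | 10% / 20% | 10% / 40% | 27.3% | 33.3% | +6.1 | 0.0 |
| E | 10% / 30% | 10% / 20% | 30.0% | 27.3% | −2.7 | 0.0 |
| F | 10% / 30% | 10% / 10% | 30.0% | 25.0% | −5.0 | 0.0 |
| G | 10% / 30% | 10% / 30% | 30.0% | 30.0% | 0.0 | 0.0 |

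Worked examples:
- Case A, intervention: 0.25×0.95 / (0.25×0.95 + 0.75×0.70) = 0.2375/0.7625 = 31.1%.
- Case B, intervention: 0.2375/(0.2375 + 0.60) = 0.2375/0.8375 = 28.4%.
- Case C, control: 0.20/(0.20 + 0.525) = 0.20/0.725 = 27.6%.
- Case F, control: 0.225/(0.225 + 0.525) = 0.225/0.75 = 30.0%.

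In every case the planned comparison would show close agreement. Case G shows that, with no true effect, an equal pattern of loss leaves the difference at zero.

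**Step 4: missing counted as non-use is not a safe default.** In cases A to C it leaves 0.25×0.95 − 0.25×0.80 = 23.75% − 20.0% = +3.75 points with no true effect. If loss is unrelated to use but is 5% in one arm and 20% in the other, complete cases are unbiased (25% versus 25%) and this rule creates the same +3.75 points.

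**Step 5: observed 25% versus 40%.** Complete-case and missing-at-random results are both +15.0 points. Counting missing women as non-users gives 0.40(1−L_int) − 0.25(1−L_con):

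| Loss control / intervention | Missing = non-user |
|---|---|
| 10% / 10% | +13.5 |
| 20% / 20% | +12.0 |
| 20% / 10% | +16.0 |
| 10% / 20% | +9.5 |
| 10% / 30% | +5.5 |

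The extreme bounds (all missing women in one arm users, all in the other non-users) are +3.5 to +23.5 points at 10% loss in each arm, and −8.0 to +32.0 at 20%.

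**The case against.** **The analysis plan is not shown, and an article condenses.** An unstated tipping-point analysis would not by itself be a finding. The point rests on the analysis that is stated: it is put forward as the sensitivity analysis for the primary outcome, and it does not vary the assumption most in doubt.

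**It is not the only safeguard.** A reader might infer that nothing else is planned. That is not so: follow-up efforts are promised, and reasons for missing data will be recorded and described. The description could reveal loss due to stopping, but it does not carry that loss into the effect estimate.

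**A woman need not attend an interview to be measured.** Facility records are a stated source alongside exit interviews, so it would be wrong to say that uptake is known only for women who return. Whether the records show that a woman has stopped is not stated.

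**The arm mechanism is plausible, not shown.** GATHER's return visit is counseling content and is not stated to be the study's assessment visit, and BCS also includes follow-up help. The documents do not support an inference that GATHER in particular would be flattered; the direction depends on which arm loses more non-users or keeps more users.

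**It is not settled that the same women are followed.** Purposive recruitment of women visiting centers could mean fresh samples. Paired tests, adjustment for baseline use and the mention of loss to follow-up suggest a cohort. With fresh samples, the problem becomes who attends, and an analysis of women due but unseen would not apply as written.

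**This is an exploratory pilot.** With 60 per arm at 25% uptake, the standard error of the difference is √(2×0.25×0.75/60) = 7.9 points before any design effect, which is larger than the biases shown. That limits the urgency. It does not make the planned check informative.

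**Conclusion.** The point holds for uptake, in this limited form: agreement between imputed and non-imputed results would not show robustness to loss that depends on stopping a method, and no stated analysis tests for it. Under the assumed loss rates, the false difference with no true effect is roughly 3 to 6 points in either direction, against an assumed 15. It is zero if the pattern of loss is the same in both arms.

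The result rests on four assumptions: that use status affects whether a woman is observed, that the covariates explain this only weakly, that the pattern differs by arm, and that uptake is imputed under missing at random. That assumption is stated for client-reported items and is the only one given.

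Two stronger readings should be resisted. The top figure of 6.1 points (41% of 15) is not an expected size; equally plausible rates give 3.4 to 3.6, or a negative bias. Nor does the argument extend to provider competence, although the same sentence of the article covers it: a client stopping a method does not explain a missing provider assessment.

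**What to change.** Keep the planned comparison and add the following for uptake:

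1. State whether the same women are assessed at baseline, 3 and 6 months, so that women due for follow-up but not observed can be counted.
2. Fill current-use status from facility records where they contain it, before any imputation.
3. For women still unobserved, run multiple imputation with an arm-specific shift (delta) in the log-odds of use. A shift of zero in every arm reproduces the planned analysis. Report the combinations of shifts at which the conclusion on the uptake difference changes.
4. Include missing counted as non-use as one scenario in that range, and do not label it conservative.
5. Tabulate the share not observed, with reasons, by arm and time point beside the uptake result.

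If different women are sampled at each time point, steps 2 to 5 do not apply as written, and selection through attendance should be described instead.

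The cost is some wording, a few extra analysis runs and possibly a less favourable range around the uptake effect. The Results section says no outcome data had been analyzed at the article's version date of August 31, 2025. If that is still so, the addition can be prespecified.

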### Fidelity Monitoring

Adherence to the GATHER and BCS interventions will be evaluated to maintain the consistency and quality of implementation. Trained supervisors will use structured fidelity checklists derived from standardized protocols to observe a randomly selected sample (10%‐15%) of counseling sessions. In addition, service providers will complete concise self-assessment logs to record essential counseling steps and any challenges encountered. Continuous digital supervision through WhatsApp will provide real-time feedback and support. A composite fidelity score calculated from checklist ratings and observational data will be used to account for variations in intervention delivery during outcome analysis.

### Ethical Considerations

Ethical approval for data collection was obtained from the Institutional Review Board of the Health Services Academy, Islamabad, Pakistan (00010/l HSA/PhD-2022) on March 7, 2025. The study was also prospectively registered with the Australian New Zealand Clinical Trials Registry (ACTRN12625000750482) on July 16, 2025, in alignment with international standards for interventional trials.

Eligible participants will receive clear verbal and written information about the study in their preferred language. Participation will be voluntary, with the option to withdraw at any time without affecting access to services. Written consent (or a thumbprint with a witness for those unable to sign) will be obtained before enrollment. No financial compensation or reimbursement will be given to the participants, as they were enrolled during routine visits and without additional costs or travel, and the study budget did not allow for participant compensation.

All data will be anonymized, entered into SPSS, and securely stored with access limited to authorized personnel. Quality assurance measures will include double data entry and regular validation checks. Physical documents will be maintained in locked cabinets to ensure their security. Given that this is a pilot study, a formal data and safety monitoring board is not required. Instead, the study team will conduct internal monitoring to ensure compliance with the protocol, safeguard participant safety, and maintain intervention fidelity. Digital platforms such as WhatsApp will be used to facilitate ongoing supervision and feedback.

## Results

Although registration was submitted prior to commencement of the study, administrative processing by the registry was finalized on July 16, 2025, one day after the originally projected start date (July 15, 2025). The registry therefore lists the trial as retrospectively registered. Importantly, no participants were enrolled prior to registration. Recruitment of FP workers began on July 20, 2025, after the completion of concurrent national dengue and polio health campaigns that had temporarily reassigned staff.

Recruitment of clients (n=333) and 48 service providers took place between July 20 and 31, 2025, followed by face-to-face training (July 31 to August 3, 2025) and eHealth knowledge reinforcement via WhatsApp groups (August 1‐31, 2025). Preintervention client satisfaction data were collected in July 2025. As of this protocol version (August 31, 2025), the intervention has been completed, and the study is in the observational follow-up period. The first postintervention data collection was scheduled at 3 months (October 2025), with the second postintervention data collection planned at 6 months (December 2025 to January 2026). No outcome data have yet been analyzed.

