**Results:**

Delivery of the intervention is underway, and baseline data from the 333 participants have been collected. The first follow-up assessments are planned at intervals of 3 and 6 months. However, no outcome data have been obtained or analyses performed at this stage.

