##### Implementation of the Intervention

The interventional phase lasts for 3 months. During this period, training on GATHER and the BCS is given to the service providers in the interventional arms. Continuous learning is ensured through refresher courses, mentorship, and supportive supervision. Trained FP service providers will apply the enhanced counseling specific to their arm during routine practice, including during consultation sessions and follow-up care, through a structured, step-by-step guide.

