##### Effective Follow-Up Through Technologically Supportive Supervision

To enhance service provider capacity and promote lasting improvements in contraception counseling practices, the study implements a dual approach: an intensive 1-day training session followed by 3 months of supportive supervision combining in-person oversight with technology-assisted follow-up. The 1-day training aimed to quickly establish core knowledge and practical skills in client-centered, rights-based contraception counseling. We acknowledge that a single training event is typically inadequate for sustained behavioral change; thus, we incorporated a structured system of ongoing supportive supervision. This includes regular supervisory visits, on-site mentoring, and direct observation, all intended to deliver immediate feedback, reinforce essential competencies, and address challenges encountered in real-world service delivery.

To supplement the in-person support and enhance both reach and responsiveness, the study incorporates technology-enabled supervision through the establishment of dedicated WhatsApp groups. These groups serve as active forums for peer learning, case-based discussions, and prompt problem-solving, fostering ongoing interaction among service providers, mentors, and supervisors. They enable the regular sharing of refresher materials, such as videos, infographics, and updated guidelines, and provide an interactive environment for exchanging experiences and clarifying uncertainties. By leveraging WhatsApp’s accessibility and ease of use, this approach ensures that service providers remain engaged, supported, and motivated throughout the implementation period. This hybrid model of capacity building, which integrates initial face-to-face training with sustained digital engagement and supervisory support, is proving to be both cost-effective and well suited to the context, thereby promoting strong adherence to the intervention and improving the quality and consistency of contraception counseling across the participating sites.

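### The intervention is described as underway, as three months long and as finished after one month, and neither follow-up round reaches 3 or 6 months from either possible end of it

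*Protocol article*

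**What the plan says.** All references are to the protocol article.

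**Length and status of the intervention**
- Implementation of the Intervention: "The interventional phase lasts for 3 months".
- Effective Follow-Up Through Technologically Supportive Supervision: "an intensive 1-day training session followed by 3 months of supportive supervision", given partly in person and partly through WhatsApp groups.
- Abstract, Results: "Delivery of the intervention is underway".
- Results: recruitment of clients and providers "took place between July 20 and 31, 2025"; then "face-to-face training (July 31 to August 3, 2025"); then "eHealth knowledge reinforcement via WhatsApp groups" from August 1 to 31. The section goes on: "As of this protocol version (August 31, 2025), the intervention has been completed", and places the study in observational follow-up.

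**Timing of follow-up**
- Data Collection and Analysis and Study Outcomes put the assessments 3 and 6 months after the intervention.
- Abstract, Methods, times the 3- and 6-month assessments from training.
- Results: "The first postintervention data collection was scheduled at 3 months (October 2025"), with the 6-month round in December 2025 to January 2026. Both rounds are called postintervention.

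**The concern.** A three-month programme that starts on July 31 cannot be complete on August 31, and a completed intervention is not still being delivered. The supervision section itself says that one training event is usually not enough to change behaviour and gives this as the reason for ongoing supervision. Whether one or three months were delivered therefore decides what is being evaluated and what a scale-up trial would copy.

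The follow-up labels depend on the same question. Uptake of modern methods is the primary outcome, and it is assessed at these two rounds. If the anchor is the end of the intervention, the anchor date moves by about two months according to which section is followed. A round taken while supervision is still running is not a post-intervention round, and the difference-in-differences analysis needs to know which rounds are. A result reported as six months after the intervention, but taken earlier, would make the effect look more durable than the data show.

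**Working it through.** **Inputs (all from Results unless noted).** Recruitment starts July 20. Training runs July 31 to August 3. Stated completion is August 31. Round 1 is October 1 to 31, 2025. Round 2 is December 1, 2025 to January 31, 2026. The planned phase length of 3 months comes from Implementation of the Intervention. The documents give rounds by month only, so I take the first and last calendar day of each window.

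**Method.** The target date is the anchor plus 3 or 6 calendar months. Elapsed time is days from anchor to window edge, divided by 30.4375.

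**Can the stated dates be reproduced?** Not from the end of the intervention. For the stated completion date:
- Targets: August 31 + 3 months = November 30, 2025; August 31 + 6 months = February 28, 2026.
- Round 1: 31 / 30.4375 = 1.02 to 61 / 30.4375 = 2.00 months. The window closes 30 days before the target.
- Round 2: 92 / 30.4375 = 3.02 to 153 / 30.4375 = 5.03 months. The window closes 28 days before the target.

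**All candidate anchors**

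| Anchor | 3-month target | 6-month target | Round 1 (months) | Round 2 (months) | Targets inside windows? |
|---|---|---|---|---|---|
| Recruitment start, July 20 | Oct 20 | Jan 20 | 2.40 to 3.38 | 4.40 to 6.41 | Yes, both |
| Training start, July 31 | Oct 31 | Jan 31 | 2.04 to 3.02 | 4.04 to 6.05 | Last day only |
| Training end, August 3 | Nov 3 | Feb 3 | 1.94 to 2.92 | 3.94 to 5.95 | No, 3 days short |
| Stated completion, August 31 | Nov 30 | Feb 28 | 1.02 to 2.00 | 3.02 to 5.03 | No, 30 and 28 days short |
| End of 3-month phase from July 31 (October 31) | Jan 31 | Apr 30 | -0.99 to 0.00 | 1.02 to 3.02 | No, 92 and 89 days short |
| End of 3-month phase from August 3 (November 3) | Feb 3 | May 3 | -1.08 to -0.10 | 0.92 to 2.92 | No, 95 and 92 days short |

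A negative value means that the round falls before the intervention has ended.

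**Reading the table.** The first two rows fit and the third nearly fits. The last three rows, which are the possible ends of the intervention, do not. The dates look as if they were counted from the start of training or from the July baseline. Data Collection and Analysis, Study Outcomes and the postintervention label in Results name the end of the intervention instead.

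The second window is also two months wide. The gap between rounds could be anything from 31 days (October 31 to December 1) to 122 days (October 1 to January 31).

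**The case against.** A reader might infer that the rounds fit no anchor at all. The documents do not support that. The Abstract times follow-up from training. From July 31 the last day of each window is exactly 3 and 6 months, and from August 3 the windows close only 3 days early, which dates given by month cannot be held to. Recruitment start fits as well. This objection stands, and it limits the point to follow-up counted from the end of the intervention.

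A reader might also call the time points undefined. That is too strong: nominal times and calendar windows are both given, and the anchor is inconsistent, not absent. Study Timeline refers to Figure 2 for a detailed schedule. The figure is not available here and may name an anchor.

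A third inference would be that the comparison between arms is biased. Results gives one set of round dates without distinguishing arms, so mislabelled elapsed time does not in itself bias that comparison. The damage is to labelling and interpretation. The trial is also presented as a pilot, and Limitations already warns that six months may be too short to show lasting effects.

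Finally, the status conflict may be partly loose wording. Delivery underway could refer to counselling of clients, and completion could refer to training plus the August WhatsApp period. Results does not mention in-person supervisory visits, so it does not prove that all supervision stopped in August. This softens the conflict but does not remove it, because placing the study in observational follow-up on August 31 still disagrees with three months of supervision.

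**Conclusion.** The point holds in this form. The current text gives three incompatible accounts of the intervention's length and status, and two anchors for follow-up. Counted from the end of the intervention, neither round reaches its nominal time. From August 31 the rounds fall at about 1 to 2 and 3 to 5 months. From about October 31 to November 3, the first round falls during the intervention or on its last day, and the second at about 1 to 3 months. A result labelled as six months after the intervention would therefore be at most about five months after it, and perhaps no more than three. The primary outcome's time points are inconsistently anchored.

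This assumes that the windows run over whole calendar months and that a three-month phase would start between July 31 and August 3. The documents do not show which account of the intervention is right, and no view is taken on that.

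**What to change.** - Reconcile the Abstract (Methods and Results), Implementation of the Intervention, the supervision section, Data Collection and Analysis, Study Outcomes and Results, so that all give the same intervention period, status and follow-up anchor. Check Figure 2 against them.
- State the intervention period actually delivered, with start and end dates for training, in-person supervision and WhatsApp support.
- Name one anchor date for follow-up and use it throughout.
- In the outcome definition and in reports, label each round by actual elapsed time from that anchor. Say whether any round overlaps with supervision.

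The cost is wording, and possibly a changed label or window for a round. No extra participants are needed. Results says that no outcome data have been analysed, so as of that protocol version the correction can be made before any result is known.
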